### Participants’ timeline

An overview of the schedule of enrolment, interventions, assessments, and visits for participants is given in Table 2.

**Table 2 Tab2:** Participants’ timeline

	Study period			
	Enrolment	Allocation	Post-allocation	Close-out
Timepoint	*− 5 months*	*0*	*>0–6 months*	*>6 months*
Enrolment:				
Recruitment general practices	X			
Identification patients	X			
Eligibility screen patients	X			
Informed consent	X			
Allocation		X		
Interventions:				
Educational course general practitioners			X	
Prolonged consultations			X	
Assessments:				
Patient demographics	X			
MMQ1	X	X		X
MMQ2	X	X		X
EQ5D-5L	X			X
Data on retention patients				X
Mortality data				X
Socioeconomic status				X
Paraclinical test data				X
Medication use				X
Hospital admission data				X
Ethnographic Interviews	X	X	X	X

### Power analysis and sample size

As this is a pilot trial, a formal sample size calculation is not performed. We aim to include 12 practices, each recruiting up to 15 patients per practice, amounting up to 180 patients in total. We considered this number sufficiently informative on the practicalities of delivering the intervention and collecting outcome data.

### Allocation and concealment

Unit of randomization will be the general practice so that all participating patients within the general practice receive either the intervention or care-as-usual. General practices will be randomly assigned on a 2:1 basis to either the intervention or care-as-usual group in blocks of three within each region. A block of three practices will be allocated simultaneously after completion of the baseline documentation for all study participants within the practices. Within each randomization block of 3 practices, we further randomize 1 of the 2 practices in the intervention arm to a sub-group, where the general practitioner has access to the aggregated scores of the MMQ1. The other intervention practice within the randomization block of 3, will be allocated to a sub-group in which MMQ1 scores will be concealed for the general practitioner. A computer randomized allocation sequence will be concealed until all general practices are assigned. Patients will be informed that they are allocated to the intervention arm or the control group by the research team through e-Boks.

### Blinding (masking)

All researchers working on quantitative analyses will be blinded to practice allocation. It is not possible to blind qualitative researchers as they analyze data they have collected themselves. Due to the nature of the intervention, it will not be possible to blind the participants or other members of the research team to allocation.

### Data collection before randomization

#### General practice data

Data collected about the general practices will include service number of the general practice (Danish: *ydernummer*), address, name(s) of general practitioners, number of patients registered at the practice, number of staff (including nursing staff and administrative staff).

#### Patient demographics and medical history

The following information will be recorded in REDCap by practice staff: CPR-number (Danish social security number), sex, age, ICPC-2 codes, and ICD-10 diagnostic codes. Reasons for non-eligibility will be recorded.

#### Quality of life measurements

For all recruited participants, the MMQ and EQ-5D-5L will be collected before allocation.

##### MMQ

The validated version of the MultiMorbidity Questionnaire (MMQ) encompasses two parts: MMQ1 and MMQ2. MMQ1 measures needs-based quality of life and MMQ2 measures self-perceived social inequity. MMQ1 encompasses 6 scales measuring: Physical ability (6 items); Worries (6 items); Limitations in everyday life (10 items); My social life (6 items), Self-Image (6 items); and Personal economy (3 items). The development of the items and the scales is based on the needs-based model for quality of life. MMQ2 encompasses different numbers of scales, with different numbers of items, that measure different constructs of self-perceived social inequity addressed towards five different types of contacts: general practitioners, the clinical staff at the general practice, other health professionals, the municipality employees, and finally, family, friends, and acquaintances.

##### EQ-5D-5L

The EQ-5D-5L is a standardized measure of health status developed by the EuroQol Group to provide a simple, generic measure of health for clinical and economic appraisal. The EQ-5D-5L descriptive system comprises the five dimensions: mobility, self-care, usual activities, pain/discomfort, and anxiety/depression. Each dimension has five response levels: no problems, slight problems, moderate problems, severe problems, and unable to/extreme problems. The respondent should indicate his/her health state by checking the box next to the most appropriate response level for each of the five dimensions [30].

### Data collection during the study period

#### Data from practices’ electronic medical records

From the practices’ electronic medical records, data will be recorded in REDCap by practice staff on patient characteristics, recruitment rates, response rates of consent forms, and attendance rates of patients in the intervention group. The SOFIA study’s trial research team provides support to practices and can monitor progress in each practice via REDCap in real-time.

#### Qualitative data on trial management, implementation, and program theory

Semi-structured interviews with general practitioners and staff will be conducted concerning the recruitment process, the educational course, the preparation and execution of the prolonged consultations, and at the end of the study. Observations will be performed of the information meetings with the practices, the educational course, and prolonged consultations in practice.

### End-of-study data collection

#### Mortality and morbidity data

Data on mortality and in- and outpatient hospital admissions during the study period in the participating patients will be collected from the National Patient Registries after completion of the pilot trial.

#### Response rates and quality of life measurements

For all recruited participants, the MMQ and the EQ-5D-5L will be collected at the end of the study period. Questionnaires will be either sent through REDCap to their e-Boks or by regular mail or email to participants in the intervention and control group at the end of the study period.

#### Medication

Data on the type of redeemed medication prescriptions from the 12 months before randomization and during the study period will be collected from the Danish National Health Service Prescription Database.

#### Biochemical and biometric data

Biochemical and biometric data available for the 12-month period before randomization, the study period, and up to 6 months after the study period will be collected concerning participants allocated to the intervention and control group. Electrocardiogram (EKG), serum hemoglobin A1C (HbA1c) serum HDL, LDL, and total cholesterol will be collected from a centralized clinical chemical laboratory database. Height, weight, and systolic and diastolic blood pressure values will be collected by the practice staff or the general practitioner from the electronic medical record and recorded in REDCap.

### Data management

The study will commence upon approval by the relevant Danish authorities and strictly adhere to Danish law governing medical research in humans and safeguarding of personal information of any kind. Data is stored and handled according to the General Data Protection Regulation. The study owner is responsible that all study activities comply with the Danish law on handling of personal data. The study owner is responsible that the identities of the participants are kept strictly confidential. To ensure these objectives, information that might allow identification of participants (e.g. name, CPR number, contact information) will also be encrypted and located on secure password-protected servers where all activity is subjected to transaction logging. All data that might allow identification of the participants will be stored for 25 years after termination of the study at which point it will be anonymized.

### Statistical methods

The quantitative parts of the primary objectives in this pilot study, e.g., the rate of recruitment of general practitioners and patients, retention of patients, and outcome data, will primarily contain descriptive statistics to assess the quality of these parameters: Mean (standard deviation) for continuously measured objectives, and raw count (%) for categorically measured objectives. For some objectives, the difference between the randomization groups is of interest, and this will be assessed statistically in linear or logistic regression models.

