## Methods

### Trial design

The pilot study is designed as a randomized, non-blinded, parallel-group trial. A 2:1 cluster randomization will be performed with the general practice level as the unit of randomization.

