#### Identification, eligibility assessment, and recruitment of patients with SMI

Participating practices will be instructed to collect the International Classification of Primary Care version 2 (ICPC-2) codes and ATC-codes from the electronic medical record on all patients who are registered at the practice at the commencement of the study and send these to the research team. ICPC-2 codes are routinely used in Danish medical practice.

A computer algorithm will randomly select a sample of 45 patients who fulfill the externally verifiable inclusion criteria for each participating general practice. This selection will be stratified, in that each sample of 45 patients includes 15 patients who meet diagnostic criteria B1, B2, or B3 respectively. The research team sends this list of 45 potentially eligible patients to the general practitioners. General practitioners are instructed to screen these lists for correct diagnoses. In case of uncertainty regarding diagnosis, general practitioners should contact the research team. When a diagnosis is verified by the general practitioner, the general practitioner will assess the eligibility of the listed patients according to the exclusion criteria described above. General practitioners are instructed to document any reasons for exclusions and any reasons for deviating from the exclusion criteria. General practitioners are instructed to recruit at least 2 patients from each diagnostic subgroup (corresponding to the inclusion criteria B1, B2, and B3). We employ a reimbursement limit of 15 patients per practice. Patients participating in the study will not receive financial compensation.

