##### Promoting trans-sectional care—the SOFIA handbook

Owing to the Danish organization of health care and social care into different sectors resorting under separate laws, formal trans-sectional care plans are not feasible. However, each general practitioner assigned to the intervention arm will receive a specialized handbook, specific for their municipality and regional affiliation, containing contact information of relevant social or health care actors, and helplines in case of substance abuse and an increased risk of suicide and self-harm.

##### MMQ part 1

Apart from improving physical health, the SOFIA study aims to improve the quality of life among the participants. To measure the quality of life, we use the patient-related outcome measure, MMQ. MMQ was developed for patients with multimorbidity, including SMI. In the SOFIA pilot trial, we want to examine if the simultaneous use of MMQ as a conversation tool and an outcome assessment will bias the MMQ as an outcome measure. Therefore, the general practices will be cluster-randomized in two subgroups, with 2 general practices from each region in both subgroups. All patients are asked to complete the MMQ part 1 (MMQ1) before the prolonged consultation. In the first subgroup, the relative sum-scores of six scales will be provided to the general practitioners via an electronic link. During the educational course, the general practitioners in the first subgroup are instructed on how to use the six scales’ sum-scores as a clinical conversation aid during the “patient part” of the consultation. In the other subgroup, the general practitioners will not have access to the MMQ1 scores.

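### The regression models named for comparing randomised groups make no allowance for practice, although practices are the units randomised

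*Protocol article*

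**What the plan says.** The Trial design section of the protocol article states that "A 2:1 cluster randomization will be performed with the general practice level as the unit of randomization". Allocation and concealment repeats this ("Unit of randomization will be the general practice so that all participating patients within the general practice receive either the intervention or care-as-usual") and adds that practices are allocated "in blocks of three within each region".

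On size, Power analysis and sample size says: "We aim to include 12 practices, each recruiting up to 15 patients per practice, amounting up to 180 patients in total". The recruitment section sets a lower expectation: "General practitioners are instructed to recruit at least 2 patients from each diagnostic subgroup".

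The section on MMQ part 1 describes a second practice-level randomisation within the intervention arm: "the general practices will be cluster-randomized in two subgroups, with 2 general practices from each region in both subgroups". Secondary outcome measures presents this as an equivalence comparison of mean change in MMQ1.

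Statistical methods is one short paragraph. The primary objectives are to be mainly described with means, standard deviations, counts and percentages. For an unlisted subset of objectives, "the difference between the randomization groups is of interest, and this will be assessed statistically in linear or logistic regression models". This is the only inferential method in the article. No section names a random practice effect, generalised estimating equations (GEE), cluster-robust errors, a practice-level analysis or an ICC. The Discussion takes up cluster randomisation, but only as a threat to comparability of the arms, and asks only for correction of imbalance in the definitive trial.

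**The concern.** Linear and logistic regression in their plain form treat patients as independent. Patients of one practice share doctors, staff and, here, the allocation itself, so their outcomes may be correlated. If so, the information about the arm difference comes largely from 12 practices rather than up to 180 patients. A patient-level model then gives intervals that are too narrow and rejects too often.

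The nested MMQ1 comparison is the most exposed, for two reasons. It has only 8 practices. It also aims to show equivalence, so an interval that is too narrow pushes towards the conclusion being sought. That conclusion bears on whether the MMQ1 can serve both as conversation tool and as outcome in the definitive trial, where quality of life measured by the MMQ is a primary endpoint.

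Adjusting for imbalance, the one consequence of clustering that the Discussion addresses, does not correct the variance.

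**Working it through.** **Inputs from the article.** 12 practices, at most 15 patients each, allocated 2:1 in blocks of three within two regions of 6 practices. The implied minimum per practice is 3 diagnostic subgroups × 2 = 6.

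**The plan's own figure.** 12 × 15 = 180, which reproduces. There is no stated power, significance level or ICC to reproduce.

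**Assumptions.** Two-sided 5% test, equal practice sizes, ICC from 0 to 0.10.

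**Number of units.** 6 practices per region make two blocks of three, so four blocks in all. Each block gives 2 intervention practices and 1 control, hence 8 vs 4. Within each block the 2 intervention practices are split 1:1, hence 4 vs 4.

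**Formulas.** With m patients per practice:
- design effect DE = 1 + (m − 1) × ICC
- standard error too small by a factor of √DE
- true error rate of an unadjusted test = 2 × [1 − Φ(1.96/√DE)]
- effective sample size = 12m/DE

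Example, m = 15 and ICC = 0.10: DE = 1 + 14 × 0.10 = 2.40; √2.40 = 1.55; 1.96/1.549 = 1.265; error rate = 0.206; effective size = 180/2.40 = 75.

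| m | ICC | DE | SE factor | True error rate | Effective size |
|---|---|---|---|---|---|
| 15 | 0 | 1.00 | 1.00 | 0.050 | 180 of 180 |
| 15 | 0.01 | 1.14 | 1.07 | 0.066 | 158 |
| 15 | 0.02 | 1.28 | 1.13 | 0.083 | 141 |
| 15 | 0.05 | 1.70 | 1.30 | 0.133 | 106 |
| 15 | 0.10 | 2.40 | 1.55 | 0.206 | 75 |
| 6 | 0.01 | 1.05 | 1.02 | 0.056 | 69 of 72 |
| 6 | 0.02 | 1.10 | 1.05 | 0.062 | 65 |
| 6 | 0.05 | 1.25 | 1.12 | 0.080 | 58 |
| 6 | 0.10 | 1.50 | 1.22 | 0.110 | 48 |

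**Check by simulation.** 20,000 trials per setting with no true effect, normal outcomes and 15 patients per practice. The patient-level test is the same as linear regression on arm.

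| ICC | 8 vs 4, patient level | 8 vs 4, practice means | 4 vs 4, patient level | 4 vs 4, practice means |
|---|---|---|---|---|
| 0 | 0.049 | 0.049 | 0.051 | 0.049 |
| 0.01 | 0.070 | 0.051 | 0.066 | 0.050 |
| 0.02 | 0.084 | 0.049 | 0.087 | 0.051 |
| 0.05 | 0.132 | 0.050 | 0.135 | 0.048 |
| 0.10 | 0.208 | 0.050 | 0.208 | 0.047 |

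The simulation agrees with the formula, and a t-test on practice means holds its level.

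**Degrees of freedom.** A practice-level analysis of 8 vs 4 has 12 − 2 = 10 degrees of freedom, with critical value 2.228, against 1.973 on 180 − 2 = 178. The ratio 2.228/1.973 = 1.13 widens intervals by a further 13%. Adjusting for region leaves 9. The unadjusted 4 vs 4 comparison has 8 − 2 = 6, with critical value 2.447.

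**Equivalence.** The same SE factors apply to the 4 vs 4 comparison. The probability of wrongly declaring equivalence cannot be computed, because the article gives no margin. The direction is clear: the narrower the interval, the more easily it fits inside any margin.

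**The case against.** The strongest reply is that the sentence names a model family for the type of outcome and leaves the variance open. A random practice effect or cluster-robust errors can be fitted within linear or logistic regression. The article is condensed, and an analysis plan that is not shown may specify them. A reader might infer that the trial has committed itself to ordinary regression and that its standard errors and p-values will certainly be wrong. The article does not support that. It neither says that clustering will be ignored nor states a significance level, and at an ICC of zero there is no inflation.

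Scope is limited too. A reader might infer that every between-arm result is affected. The analysis is mainly descriptive and regression applies to an unlisted subset of objectives. Care processes are assessed in the intervention practices, and the end-of-study response criterion is set for each arm without a test of difference. Nor does any section say that a between-arm significance test decides progression or sets the definitive sample size.

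A reader might also infer that the progression thresholds need clustered confidence intervals. The 20% criterion is a proportion of practices, so patients within practices do not enter it. The thresholds are descriptive prompts for re-evaluation, and a missed one does not by itself rule out feasibility.

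All of this stands and limits the claim. It does not remove it. The article is not silent on method: it names one model class which, unqualified, does not match the randomisation. Where it discusses clustering, it still leaves out the effect on variance.

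**Conclusion.** The point holds in a limited form. The only inferential method named makes no allowance for the unit of randomisation, in a comparison of 8 vs 4 practices and a nested one of 4 vs 4. If the models are fitted as written at patient level, standard errors are too small by a factor of 1.07 to 1.55 with 15 patients per practice, and of 1.02 to 1.22 with 6, over an assumed ICC of 0.01 to 0.10. The 15-patient figures are the upper end, because 15 is a cap. The practical weight falls on the nested MMQ1 comparison, where the error favours equivalence. For the rest of this mainly descriptive pilot, the consequence is confined to those objectives on which randomised groups are compared.

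**What to change.** Add to Statistical methods, in words such as these:

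> Where randomised groups are compared, including the MMQ1 sub-study, differences are estimated with the practice as the unit. Continuous outcomes are analysed with a linear mixed model with a random practice effect and small-sample degrees of freedom, or by an analysis of practice-level summaries. Binary outcomes are analysed on practice-level summaries or by GEE with a small-sample correction. Analyses adjust for region, the randomisation stratum. The ICC of the MMQ and EQ-5D-5L scores is reported.

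The stated degrees of freedom must match the adjustment. For practice-level summaries they are 10 for 8 vs 4 unadjusted and 9 with region, and 6 for 4 vs 4 unadjusted. Each further practice-level covariate, such as a baseline mean, costs one more.

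Reporting the ICC also serves the pilot's aim of informing the definitive trial's sample size, although an estimate from 12 practices will be imprecise.

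The cost is a few sentences and somewhat wider intervals. No new data are needed. If an analysis plan already specifies such methods, a reference to it in this section is enough.

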### Qualitative methods

Interviews will be recorded and transcribed, and notes will be taken systematically during observations. All qualitative data will be analyzed with qualitative methods ensuring a systematic and transparent approach and several researchers will cooperate and reach a consensus of the coding structure and analysis of the data. The software program NVivo will be used in the process of coding and analysis.

### Data monitoring

Due to the short duration of the trial and minimal health risks for the participating practices and patients, no formal data monitoring committee will be used. Interim analyses and auditing will not be performed.

### Harms

The study aims to improve the overall health and quality of life for a group of Danish citizens that are currently not receiving the indicated treatment for common conditions, and who experience the highest level of inequality and inequity in healthcare. The value of the study lies in its ability to identify and treat or support people with multiple conditions and to provide them with the appropriate clinical care to reduce the risk of premature death from untreated or undertreated somatic conditions.

A potentially harmful effect of our study is overdiagnosis. Since the study aims to identify and treat undiagnosed conditions, certain deviations, abnormalities, risk factors, or pathologies may be detected that were never going to cause harm. The limited sample size of the pilot trial prevents appropriate analyses of any potential harms and will therefore not be performed.

We expect that neither acceptance nor rejection from patients to participate in the study will affect the quality of clinical treatment by their general practitioner. The general practitioners that are allocated to the intervention arm will have received training in working with patients with SMI. Hence, it is anticipated that the care for the patients that do not wish to participate is better relative to the treatment they would have received otherwise.

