***FI*****nd any symptoms for undiagnosed or undertreated somatic diseases: The “general practitioners’ part” of the consultation** The middle section of the consultation aims to collect information on current diagnoses and their treatments and to detect possible, unrecognized, and undertreated disorders or overdiagnosed and/or overtreated conditions. The general practitioners are instructed to ask about known diseases and current treatments and any symptoms that the patient may experience. The general practitioners will perform a focused physical somatic diagnostic interview, based on any somatic concerns that the patient and general practitioner agree upon. The patient must be physically examined, even if the patients have no physical complaints, because of the delayed and altered bodily experience often accompanying SMI. The general practitioners conclude this part of the consultation with a brief review of current medication and, if relevant, make a plan to optimize pharmacological treatment. The general practitioners discuss adherence challenges related to treatment, possible side effects, and any possible considerations or wishes for medication changes with the patient. If required, a pharmacologist can be consulted by email. If required, a follow-up consultation focusing on medications will be scheduled.	
***A*****gree on individual care plan (final step of the SOFIA consultation)** During the final part of the consultations, an individual care plan is made. The general practitioner and the patient will discuss current treatment with the patient, i.e., is the patient adequately treated for his/her current conditions. The general practitioner and patient assess whether treatment adjustments are needed. The general practitioner explores if anything discussed during the consultation requires follow-up, i.e., referrals to municipality or psychologist, or referral to “institutional care facility” or other services as provided by the SOFIA handbook. The general practitioner creates a safety-net—by emphasizing that the patient is always welcome to contact the practice. If medically indicated, paraclinical tests and follow-up consultations will be scheduled.	

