All patients, regardless of allocation, will complete the two outcome questionnaires the MMQ and the EQ-5D-5L questionnaire at baseline, after randomization, and at the end of the pilot trial. Based on the number of returned questionnaires, we will calculate response rates and the proportion of missing data in each completed questionnaire. We set a minimum acceptable threshold for the response rate before randomization of both questionnaires at >90% with a maximum proportion of missing data at <10%. We set a minimally acceptable response rate at >90% for both questionnaires at the end of the study period in both the intervention and the control group.

Data on mortality and in- and outpatient admissions during the study period in the participating patients will be collected from the national patient registries after completion of the pilot trial. These data, along with the scores of the MMQ, and the EQ-5D-5L questionnaires, will be used to estimate the necessary sample size to power the definitive trial, which primary endpoints are mortality and quality of life, as measured by the MMQ.

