Concerning the program theory, we will assess selected proposed connections, mechanisms, and contextual conditions influencing intervention implementation and outcomes, mainly to gain a preliminary indication of the effectiveness of the prolonged consultations (change in diagnosis, medication, referrals, increased contact) and the effectiveness of the educational course in changing the clinical practice approach. This can give rise to elaborations of the program theory and adjustments of the intervention before the definitive trial. These issues will be assessed by a combination of the registrations in REDCap, observations, and interviews with practices in the intervention group. Furthermore, we will conduct interviews in all allocation groups on usual care and in the control group on the non-study care they have received during the study period.

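### The sample-size reason given for doing no harms analysis rules out formal comparison but not descriptive counts, and the same sample is accepted for a preliminary indication of effectiveness

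*Protocol article*

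**What the plan says.** Three parts of the protocol article bear on this.

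- **Harms.** The section states "A potentially harmful effect of our study is overdiagnosis" and gives the mechanism: "certain deviations, abnormalities, risk factors, or pathologies may be detected that were never going to cause harm". It ends with the rule "The limited sample size of the pilot trial prevents appropriate analyses of any potential harms and will therefore not be performed".
- **Secondary outcome measures, item 3 (programme theory).** Selected connections and mechanisms are to be assessed "mainly to gain a preliminary indication of the effectiveness of the prolonged consultations (change in diagnosis, medication, referrals, increased contact"). The sources follow: "These issues will be assessed by a combination of the registrations in REDCap, observations, and interviews with practices in the intervention group". Interviews on usual care in all groups, and on non-study care in the control group, are added.
- **Statistical methods.** For the quantitative parts of the primary objectives the plan is mainly descriptive, with counts and percentages for categorical measures. Regression models are kept for those objectives where a difference between randomised groups is of interest.

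Deaths and hospital admissions (Primary outcome measures, item 3; Mortality and morbidity data) and redeemed prescriptions (Medication) are to be obtained from national registers, with no restriction to one arm. The Data monitoring section provides for no monitoring committee, interim analysis or audit.

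**The concern.** The reason given does not carry the rule built on it. A small sample is grounds for not testing. It is no grounds for leaving out a table of what happened to participants, yet the sentence covers every analysis of every potential harm.

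The same sample is treated differently on the benefit side. Altered diagnoses, medication and referrals in these patients are taken as a first sign that the consultation works. Overdiagnosis, the harm the protocol itself names, would appear among those same events, and no criterion is given to separate a warranted new diagnosis from an unneeded one.

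At stake is what the pilot can report before a larger trial in a vulnerable group. With no monitoring committee or interim look, end-of-study reporting is the main quantitative place where a signal could surface. As written, the protocol disclaims any harms report there.

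**Working it through.** The point is mainly one of logic. The arithmetic only shows what a descriptive table could and could not deliver.

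**1. Reproduce the planned size.** From Power analysis and sample size: 12 practices × up to 15 patients = 180, as stated. From Allocation and concealment: 2:1 in blocks of three within region. Six practices per region give 4 intervention and 2 control in each, so 8 and 4 overall. That is up to 8 × 15 = 120 and 4 × 15 = 60 patients. No formal sample size, alpha or power is stated.

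**2. Is a formal harms comparison weak at this size?** The documents give no event rate or intracluster correlation (ICC), so both are assumed here: a 20% event proportion in each arm and an ICC of 0, 0.05 or 0.10. The design effect is DE = 1 + (m − 1) × ICC, where m is patients per practice. The 95% half-width is 1.96 × √[0.2 × 0.8 × DE / 120] for the intervention arm and 1.96 × √[0.2 × 0.8 × DE × (1/120 + 1/60)] for the difference.

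| ICC | DE (m = 15) | Intervention arm | Difference between arms |
|---|---|---|---|
| 0 | 1.0 | ±7.2 points | ±12.4 points |
| 0.05 | 1.7 | ±9.3 points | ±16.2 points |
| 0.10 | 2.4 | ±11.1 points | ±19.2 points |

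Fifteen per practice is a reimbursement cap. The instructed minimum is 2 in each of 3 diagnostic groups, or 6 per practice, which gives 48 and 24 patients. The half-width of the difference is then 1.96 × √[0.16 × (1/48 + 1/24)] = ±19.6 points at ICC 0. With DE = 1 + 5 × 0.05 = 1.25 it is ±21.9 points, and with DE = 1 + 5 × 0.10 = 1.5 it is ±24.0 points. With only 12 practices the normal approximation is, if anything, optimistic. A formal comparison would indeed be weak.

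**3. Does that rule out counts?** No. Counts and percentages need no power, and the Statistical methods section already uses them elsewhere.

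**4. Set the two uses of the sample side by side.**

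| | Harms | Secondary outcome, item 3 |
|---|---|---|
| Events | findings that would never have caused harm | altered diagnoses, medication, referrals; more contact |
| Same patients | yes | yes (intervention arm) |
| Sample judged adequate | no, for any analysis | yes, for a preliminary indication |
| Direction stated | – | only for contact |

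**5. What data exist by arm?** Deaths, admissions and redeemed prescriptions are collected without restriction to one arm. Diagnoses and referrals during follow-up are not in the list under Data from practices' electronic medical records, and item 3 ties its sources to intervention practices. Control-arm counts of those two cannot be assumed.

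**The case against.** The strongest reply is that the protocol's caution is right: contrasts of ±12 to ±24 points cannot settle whether the intervention harms anyone, and overdiagnosis cannot be read off a count of diagnoses. Item 3 is secondary, is labelled preliminary, has no progression threshold, and draws on observation and interviews that may supply context. All of this stands, and it limits the weight of the point. It does not defend a sentence that excludes description along with testing. Nor can the matter be left to an unseen analysis plan, because the protocol makes an explicit statement.

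Four stronger readings are tempting, and the documents do not support them.

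- *A rise in diagnoses would be read only as success.* The text speaks of change and states a direction only for contact. Table 1 asks the general practitioner "to detect possible, unrecognized, and undertreated disorders or overdiagnosed and/or overtreated conditions", so a change may equally be the removal of a diagnosis or drug.
- *Using deaths and admissions to size the definitive trial contradicts the Harms section.* It does not. Event frequency as a design input is a different task from judging whether the intervention caused harm.
- *Seeing zero events in 120 patients would exclude a meaningful risk of the named harm.* Such a bound needs an event that can be recognised when it occurs. Overdiagnosis is not one, and zero new diagnoses is implausible in consultations meant to find them.
- *No by-arm view of deaths or admissions will ever be produced.* The protocol rules out a harms analysis. It does not bar tabulating these data for other purposes.

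**Conclusion.** The concern holds in a limited form. The Harms sentence is broader than its reason: the planned sample prevents a useful formal comparison but not a descriptive account. The same sample is accepted for a preliminary indication of effectiveness from a direction-free measure that would also contain unneeded diagnoses and has sources centred on the intervention arm. No primary feasibility result is affected and no stated figure is wrong, so the weight is moderate: a cheap correction worth making before reporting. The logic depends on no assumed number. The half-widths rest on the assumed 20% event rate and ICC of 0 to 0.10 and serve only to show that the table should be descriptive.

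**What to change.** In **Harms**, replace the final sentence of the overdiagnosis paragraph with wording such as: *No formal tests for harm are done. Deaths, in- and outpatient admissions and changes in redeemed prescriptions are tabulated by arm (n, %). New diagnoses and referrals are tabulated where data exist, at least in the intervention arm.* Because the prescription look-back is 12 months and the study period is 6 months, the table should say how the two windows are made comparable.

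In **Secondary outcome measures, item 3**, describe altered diagnoses, medication, referrals and contact as process measures, neutral in direction, rather than as an indication of effectiveness.

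The cost is one extra table, largely from register data already planned, and two wording changes. The downside is that between-arm contrasts will be imprecise and should be labelled so. Counts alone cannot identify overdiagnosis; they show only the volume of change and, where both arms have data, whether it differs.
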